## Abstract

**Introduction:**

Oral emergency contraception (EC) can prevent unintended pregnancy but it is important to start a regular method of contraception. Women in the UK usually access EC from a pharmacy but then need a subsequent appointment with a general practitioner or a sexual and reproductive health (SRH) service to access regular contraception. Unintended pregnancies can occur during this time.

**Methods and analysis:**

Bridge-It is a pragmatic cluster randomised cohort cross-over trial designed to determine whether pharmacist provision of a bridging supply of a progestogen-only pill (POP) plus rapid access to a local SRH clinic, results in increased uptake of effective contraception and prevents more unintended pregnancies than provision of EC alone. Bridge-It involves 31 pharmacies in three UK regions (London, Lothian and Tayside) aiming to recruit 626–737 women. Pharmacies will give EC (levonorgestrel) according to normal practice and recruit women to both intervention and the control phases of the study. In the intervention phase, pharmacists will provide the POP (desogestrel) and offer rapid access to an SRH clinic. In the control phase, pharmacists will advise women to attend a contraceptive provider for contraception (standard care).

Women will be asked 4 months later about contraceptive use. Data linkage to abortion registries will provide abortion rates over 12 months. The sample size is calculated on the primary outcome of effective contraception use at 4 months (yes/no) with 90% power and a 5% level of significance. Abortion rates will be an exploratory secondary analysis. Process evaluation includes interviews with pharmacists, SRH clinicians and women. Cost-effectiveness analysis will use a healthcare system perspective and be expressed as incremental cost-effectiveness ratio.

**Ethics and dissemination:**

Ethical approval was received from South East Scotland REC June 2017. Results will be published in peer-reviewed journals and conference presentations.

**Trial registration number:**

ISRCTN70616901.

Strengths and limitations of this studyExamines the important outcome of abortion rates over 1 year as an exploratory secondary analysis.Applicable only to women receiving levonogrestrel emergency contraception (EC), followed by a desogestrel progestogen-only pill (POP).Not applicable to use of ulipristal acetate for EC, since hormonal methods of contraception, such as the desogestrel POP, may interact with efficacy of ulipristal acetate, if started within 5 days.

## Introduction

Unintended pregnancy is widely perceived as a major public health problem. Unintended pregnancy commonly ends in abortion and the UK has among the highest abortion rates in Europe.^1^ In 2017, almost 200 000 pregnancies ended in induced abortion.^2 3^ Unintended pregnancy also ends in childbirth; around 10% of UK births are unintended and 25% mistimed.^4^ Unintended pregnancy is costly to the National Health Service (NHS) (estimated to cost over £1 billion annually)^5^ and can be distressing for women. Unintended pregnancies are more common in young women from deprived backgrounds, contributing to widening health inequalities for both mother and baby, and their families.^2 3^ Unintended childbirth can have both socioeconomic consequences for women and their families and mental health consequences.^6^

Oral emergency contraception (EC) prevents pregnancy in individual women following unprotected sex or contraceptive accidents. EC is only effective if taken before ovulation as it works by inhibiting or delaying ovulation.^7^ Since EC became available from pharmacies in the UK without the need for a prescription, there has been a change in the pattern of access such that women who seek EC now choose to obtain this from a pharmacy rather than a contraceptive provider such as a general practitioner (GP) or sexual and reproductive health (SRH) service.^8^ Although trials have shown that this facilitates access to EC and increases use, they have failed to show that this reduces unintended pregnancy rates within the population.^9^

There are two types of EC: the most widely used EC contains the progestogen levonorgestrel and should be taken within 72 hours of sex; the other EC contains the progesterone receptor modulator ulipristal acetate and should be taken within 120 hours of sex.^10^ Neither formulation of EC prevents conceptions from subsequent acts of sex and the risk of pregnancy is increased up to threefold among women who have further unprotected sex in the same menstrual cycle after using EC than those who do not.^10^ An effective method of contraception should, therefore, be started as soon as possible.^10 11^ However, the only contraceptives that can be obtained from any pharmacy without a prescription are condoms, which have high failure rates.^12^ This means that women usually need to make an appointment with a contraceptive provider (GP or SRH) and may experience delays in accessing regular contraception or lose the motivation to access a regular method altogether, which in turn may result in unintended pregnancies. In addition, although pharmacists in the UK are supposed to advise women on where to obtain ongoing contraception after EC, in one study fewer than half of pharmacists did so.^13^ It is possible that if pharmacists could supply a temporary (bridging) method of contraception to women along with EC, this would bridge the gap until women could get an appointment with a contraceptive provider for contraceptive advice and supplies. The progestogen-only pill (POP) is an effective method of contraception with few contraindications^14^ making it safer than the combined contraceptive pill/oral contraceptives for pharmacy provision. However, studies have shown that starting hormonal contraception containing a progestogen within 5 days of ulipristal acetate may reduce the efficacy of EC and so only EC containing levonorgestrel is suitable for use in conjunction with a bridging method of hormonal contraception in this way.^15 16^

### Pilot

In a pilot study in Edinburgh of 168 women presenting for EC,^17^ 11 pharmacies were randomised to one of three groups to provide EC (levonorgestrel) and either (1) standard advice on where to obtain ongoing contraception or (2) 1 month of a POP or (3) the offer of rapid access to a local SRH service. Participants were contacted by telephone 6–8 weeks later to determine their current contraceptive use. Compared with standard care, the proportion of women using effective contraception was significantly greater in both the POP (56% vs 16%, p=0.001) and the rapid access groups (52% vs 16%, p=0.027). This suggests that a supply of 1 month of POP after EC or rapid access from a pharmacy to an SRH service might increase short-term uptake of effective contraception following EC.

We now propose a large randomised trial to determine whether a pharmacy-based intervention designed to facilitate the uptake of effective contraception after EC increases use of effective contraceptive methods including the most effective long-acting reversible contraceptive methods (LARC) such as the contraceptive implant and intrauterine contraception^12^ at 4 months when compared with standard care. We will examine contraceptive uptake at 4 months as most POP preparations are packaged as a 3-month supply and so by 4 months the pharmacy provided supply will have ended.

### Aim

The aim is to develop a simple and affordable intervention which facilitates the uptake of effective ongoing contraception among women obtaining EC from pharmacies thereby reducing unintended pregnancy. The primary objective is to determine whether offering women attending a pharmacy for EC, a 3-month bridging supply of POP plus the offer of rapid access to a local SRH service results in increased uptake of effective contraception. The study POP (desogestrel) is commonly used in the UK. In contrast to other POP s, the desogestrel POP reliably inhibits ovulation and has similar effectiveness to a combined hormonal contraceptive pill/oral contraceptives (COCP), yet fewer contraindications than a COCP.^14 15^ This combined intervention (POP plus rapid access) offers both a highly safe temporary method of contraception and facilitates access to a specialist contraceptive service where all methods of contraception including the most effective LARC methods can be provided. If this intervention leads to increased uptake of effective contraception including LARC methods compared with standard care alone then we might expect that this would translate into fewer unintended pregnancies for women.

## Methods and analysis

### Study design and setting

A pragmatic cluster randomised cohort cross-over trial with cost-effectiveness including process, outcome and economic evaluation involving 31 pharmacies in three UK regions (15 in London (South and Central), 12 in Lothian (Edinburgh and region) and 4 in Tayside (Dundee and region).

### Patient and public involvement

The members of the patient and public involvement (PPI) group at the SRH service in Edinburgh contributed to the design of this study. The study protocol and documentation were reviewed and approved by the chair and members of the PPI group. The plain English summary was edited by a PPI member and improved as a result. There are three PPI members that participate and contribute to the Bridge-It Trial steering Committee meeting that provides oversight of the study. PPI group will be involved in the dissemination of the study results.

### Intervention

The planned intervention is a composite intervention. Each woman in the intervention phase will receive 3 months of POP (in a single package covering 3 months) and an invitation to attend a local participating SRH service to discuss and obtain effective contraception (including LARC methods). Three packets of POP, (75 mcg desogestrel; UK) containing 28 tablets each will be provided at no cost to women as a bridging method of contraception, providing them with 3 months of contraception during which time they can get an appointment with a contraceptive provider to obtain their preferred method of contraception. Locally approved patient group directions (ie, strict criteria to permit provision of specified medicines by non-prescribers) will permit participating pharmacists to dispense the POP to women recruited to the study. Prestudy training will be undertaken with participating pharmacists including identifying medical contraindications to POP, potential drug interactions medications and ‘missed pill’ guidance for POP. Pharmacists will advise women to start the POP the day following intake of EC^10^ and provide women with a patient information booklet on the POP from the family planning association (www.fpa.org).

Pharmacists will encourage women to attend the participating local SRH service to obtain the contraceptive method of their choice. Participants (intervention phase) will be given a study card to alert staff at SRH services that they are in the Bridge-It study and should be seen as a drop in for contraception that same day. This card will also provide written information about the location and opening hours of the local participating SRH service. These SRH services are within a 5 mile radius of the participating pharmacies and provide all methods of contraception at no cost as is the norm in the NHS.

### Standard care

A mystery shopper exercise^13^ will be undertaken in all 31 participating pharmacies to characterise ‘standard care’ (usually verbal advice to visit a clinic for contraception, with/without written and verbal information) in the control phase. The mystery shopper visits will be conducted when the pharmacy is not recruiting and just before the control phase starts. The mystery shoppers and the scenario used will be chosen by the PPI group. A simple scenario relating to request for EC will be used. Immediately after leaving the pharmacy, the mystery shopper will complete a standard data collection proforma, recording any information given by the pharmacist about use of contraception after taking EC, including provision of written information.

### Participants

We will recruit a total of 626–737 women presenting for EC. The final number will be determined based on the observed ratio of the between-period within-cluster correlation (BPC) and the within-period within-cluster correlation (WPC)—with the larger sample size (near the 737 upper limit) required for values of BPC close to zero, and the smaller sample size (near the 626 lower limits) required for values of BPC close to WPC.^18^ Each pharmacy will be expected to recruit an average of 12–13 women to the intervention arm and 12–13 women to standard care. This allows for a 25% lost to follow-up at 4 months (missing data on primary outcome).

### Randomisation

Each pharmacy will be randomised to either the intervention phase for approximately 20 weeks followed by standard care phase for 20 weeks or vice versa with a washout period of 2 weeks between the two phases. The order in which pharmacy allocation to each arm is undertaken (intervention or control first) will be randomised (figure 1). The order of delivery of intervention or control for each pharmacy was randomised for this cluster cross-over design from a randomisation file prepared by the study statistician in the Data Centre at the Centre for Healthcare Randomised Trials (CHaRT), University of Aberdeen, using SAS V.6.4 for Windows. The method used for generating the random unpredictable mix of permuted blocks was a computer software algorithm that randomly allocated blocks of size 2, 4 and 6; blocking was used to ensure balanced group sizes.

**Figure 1 F1:**
[figure not shown]
Bridge-it flow chart. POP, progestogen-only pill; SRH, sexual and reproductive health.

This is a cluster cohort cross-over design so it is the pharmacy that is the unit of randomisation and the 'cross-over' means that we are just randomising the order that each pharmacy gives the intervention in. The ‘cohort’ label means that we expect different women to be recruited within each site in the two periods (intervention and control phases).

### Recruitment

The pharmacist will assess medical eligibility of women presenting for EC for the study, provide EC according to normal practice and invite eligible women to participate. A detailed patient information sheet will be provided to all women and informed consent will be obtained by participating community pharmacists. The EC used in this study is levonorgestrel and will be given in the clinically indicated dose for the woman’s weight (1.5 mg or 3 mg levonorgestrel).^10^

Inclusion and exclusion criteria are shown in box 1. Women who give written consent will be recruited in the study. We recognise the importance of participant retention and will offer a voucher of £10 at recruitment.^19^

Box 1Inclusion and exclusion criteriaInclusion criteriaIntake of EC (levonorgestrel).Capacity to give informed consent to participate in the trial which includes adherence to trial requirements.Age 16 years or over.Willing to give contact details and be contacted at 4 months by phone or text or email or post.Willing to give identifying data sufficient to allow data linkage with NHS registries.Exclusion criteriaContraindications to the progestogen-only pill (POP).On medication that interacts adversely with POP.Already using a hormonal method of contraception.Require interpreting services.If pharmacist has concerns about non-consensual sex.EC, emergency contraception; NHS, National Health Service.

### Outcomes

A full list of study outcome measures is included in table 1. Outcomes at 4 months will primarily be collected via telephone interviews or via web-based questionnaires. However, participants will also have the option to provide the same information by a postal questionnaire. The primary outcome is use of effective contraception at 4 months (intervention vs standard care).

**Table 1 T1:** Study outcomes

	Data source
Main outcome	
Use of effective contraceptive method (hormonal or intrauterine) in intervention versus control at 4 months	Self-reported (telephone or self completed survey) at 4 months
Secondary outcomes	
Numbers undergoing an abortion within 12 months intervention versus control	National abortion registries
Economic evaluation	Incremental cost-effectiveness ratio for pregnancies prevented

Secondary outcomes are proportion of participants having an abortion within 12 months of EC use using record linkage from participants to national registries and cost-effectiveness.

### Process evaluation measures

A process evaluation will be conducted as part of the study to assess potential issues concerning intervention implementation, the causal mechanisms of impact and the contextual factors that could affect these. The process evaluation will comprise of quantitative and qualitative data measures, as detailed in box 2.

Box 2Process evaluation methods and dataTheoryTheory of change modelStudy teamPharmacy recruitment forms (study team members involved in recruitment will routinely record decision-making contributing to pharmacy selection, including: number of contacts made; responses from potential pharmacists; rationales for inclusion/exclusion and reasons for refusal).PharmacistsParticipant observation of training and review of training and intervention materials.Recruitment monitoring forms (n=100% of pharmacists) and protocol adherence checklists (n*=*100% of pharmacists).Follow-up semistructured telephone interviews with pharmacists (n=27; one with each pharmacy involved).Sexual and reproductive health (SRH) providersSemistructured telephone interviews with SRH providers (n=12; with service manager, mix staff at 2x services in London; 1x service in Edinburgh; 1x service in Dundee).ParticipantsTelephone questionnaire administered by research nurse at 4 months postintervention (n=100% participants).Semistructured telephone interviews at 4 months postintervention (n=60; 22 in London, 30 in Edinburgh and 8eight in Dundee).ContextAudit of local contraceptive services within 10 miles of study sites in London, Edinburgh and Dundee.Monitoring of contemporaneous events, such as relevant high coverage media stories using Google Alerts.

### Data collection

#### Quantitative data

Participant flow: Participant flow through the study will be assessed and reported following the Consolidated Standards of Reporting Trials flow chart.

#### Baseline

Participant demographics and reproductive history is collected at recruitment by a self-administered paper questionnaire given to them by the pharmacist. Demographic data will also be reported for the process evaluation, protocol adherence checklists and for recruitment screening forms (see box 2).

#### Contraceptive use at 4 months

This will be based on self-reported data from women at a telephone follow-up interview with a research nurse at 4 months after obtaining EC. If participants prefer, the questions can be self-completed by a web-based questionnaire or paper questionnaire sent by the post. Women will be asked what method of contraception they are using (if any), if they attended a GP or SRH service for this, if they used the POP (intervention phase only) and their pregnancy status. If pregnancy has occurred since EC then the validated London Measure of Unintended Pregnancy tool will be administered to measure intended-ness of the index pregnancy^20^ (table 1).

#### Abortion rates at 12 months

Information Services Division (Scotland) and Department of Health (England) will provide the number of abortions occurring during the 12-month follow-up period in each arm by conducting linkage of the identifiers (collected at baseline) from study participants.

#### Validation

We will check with data from local SRH services to determine the numbers of participants from intervention and control phases who attend the local participating SRH service, and which method of contraception they received.

#### Qualitative data

Semistructured, qualitative telephone interviews of a purposive sample of up to 60 women who received the intervention (approximately 22 in London, 30 in Edinburgh and 8 in Dundee) will be undertaken. Participants who consent to these telephone interviews will be contacted by the Process Evaluation Research Assistant. Interviews will explore experience of intervention acceptability in more depth and assess experiences of bridging from EC to regular contraception, and reasons for doing so or not (Box 2). Interviews will be conducted soon after the 4-month follow-up.

Interviews with 27 pharmacists and 12 SRH service providers will explore their perceptions of barriers and facilitators to implementation and more broadly, their views on the intervention, the trial and the target population. Interviews will be conducted by the process evaluation research assistant soon after the intervention phase has completed.

For the process evaluation, data collection also includes: review of training and materials, observation of training, mapping of local contraceptive services within 10 miles of study sites and monitoring of contemporaneous events, such as relevant high coverage media stories using Google Alerts (box 2).

### Sample size calculation

The study is a pragmatic cluster randomised cohort cross-over trial. Ideally the control and intervention phases should be of roughly equal duration and size, and the sample size is calculated assuming an equal cluster size in both control and intervention periods, and equal across sites (the expected site/period average). In practice, there is variability in EC demand across sites and over time, for example, demand is affected by peak holiday periods (recruitment decreases) and student term times (recruitment increases); and the ability of a pharmacy to translate that variable demand into study recruits depends on many factors, including changes to circumstances at individual pharmacies or loss of/change of pharmacists at multipharmacist stores.

Informed by our pilot study, we have assumed that effective contraception use in the control would be 30% and we were likely to achieve a 50% relative improvement to 45%. This means the sample size is in the range 626–737, assuming 25% of women do not provide 4-month contraceptive use data, and an average cluster size of 12–13 in each period, and around 25 pharmacies taking part, with 90% power and a 5% level of significance. The uncertainty in the required sample size rests on the assumed BPC and its relationship to the other component of variability, the WPC.^18^ The WPC is the usual correlation (known as the intraclass correlation in a standard parallel groups non-cross-over cluster setting) of two individuals’ outcomes within a cluster (in the same period). The BPC on the other hand is the correlation between two individuals’ outcomes in the same cluster between the two periods. If the BPC is zero, there is no advantage in a cross-over design over the standard parallel groups cluster design; if the BPC equals the WPC then the crossover is as efficient as an individually randomised design. We will finalise the sample size depending on the observed ratio of the BPC to WPC, and the observed rate of attrition, but still assuming the same control rate and treatment effect, once we have 4-month data on at least 500 participants.

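### The stated pharmacy count and per-period recruitment do not match the 626–737 range or the 31-pharmacy design

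*Protocol article*

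**What the plan says.** The Sample size calculation section gives a range of 626–737 women for 30% against 45% effective contraception use, "with 90% power and a 5% level of significance", and 25% of women without 4-month data. It names the cluster inputs as "an average cluster size of 12–13 in each period, and around 25 pharmacies taking part".

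The Participants section repeats the range and turns the cluster size into a site target: "Each pharmacy will be expected to recruit an average of 12–13 women to the intervention arm and 12–13 women to standard care". It adds that this figure already covers 25% loss to follow-up, so 12–13 means women recruited, not women analysed. The same section places the end near 737 at a between-period correlation (BPC) close to zero. It places the end near 626 at a BPC close to the within-period correlation (WPC).

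Study design and setting describes a trial "involving 31 pharmacies in three UK regions", and the abstract and the Standard care section also give 31. Trial status reports 29 recruiting sites in February 2019. Box 2 of the process evaluation plans pharmacist interviews as "n=27; one with each pharmacy involved".

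**The concern.** The total, the number of pharmacies and the recruits per pharmacy per period are tied by a simple product, so any two fix the third. The article states all three, and they do not agree with each other or with the number of pharmacies in the design.

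Two things depend on this. The first is the site target: a pharmacy told to recruit 12–13 per period is working to a total that is either below the upper limit (at 25 pharmacies) or above it (at 31). The second is the basis of the stated power. The design effect of a cluster cross-over trial depends on the cluster-period size, so a range quoted for one combination of count and size does not carry over unchanged to another. The article also plans to fix the final total from the observed BPC/WPC ratio and attrition once at least 500 women have 4-month data, and that step needs the right cluster-period size.

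**Working it through.** **Inputs.** Range 626–737, 12–13 recruits per period, around 25 pharmacies, 25% attrition, 30% v 45%, 90% power and 5% significance (Sample size calculation); 12–13 as recruited women (Participants); 31 pharmacies (Study design and setting); 29 sites (Trial status). Two periods throughout. Two-sided testing is assumed, as the article does not state it.

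**Step 1: the plan's own product.** Total = pharmacies × 2 × recruits per period.

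| Pharmacies | Total at 12–13 per period | Per period needed for 626 | Per period needed for 737 |
|---|---|---|---|
| 25 | 25 × 2 × 12 = 600 to 25 × 2 × 13 = 650 | 626/50 = 12.5 | 737/50 = 14.7 |
| 29 | 29 × 2 × 12 = 696 to 29 × 2 × 13 = 754 | 626/58 = 10.8 | 737/58 = 12.7 |
| 31 | 31 × 2 × 12 = 744 to 31 × 2 × 13 = 806 | 626/62 = 10.1 | 737/62 = 11.9 |

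The lower limit is reproduced: 25 × 2 × 12.5 = 625. The upper limit is not: 737 − 650 = 87 women. Reaching 737 at 12–13 per period takes 737/26 = 28.3 to 737/24 = 30.7 pharmacies, that is about 28–31.

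**Step 2: can any single count work?** The range spans a ratio of 737/626 = 1.18, and the per-period figure spans 13/12 = 1.08. With a fixed number of pharmacies, 12–13 therefore cannot cover both ends. Twenty-five fits only the lower limit, 29 only the upper, and 31 neither.

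**Step 3: is 12–13 perhaps the analysed number?** Then 25 pharmacies would recruit 600/0.75 = 800 to 650/0.75 = 867 women, which also misses the range. The Participants section excludes this reading in any case.

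**Step 4: is the lower limit sound on statistical grounds?** An individually randomised comparison of 30% with 45% needs 217 per arm without continuity correction: 434 analysed, 434/0.75 = 579 recruited. With the correction it needs 230 per arm: 460 analysed, 460/0.75 = 614 recruited. The second figure is 12 women (2%) below 626.

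**Step 5: can both limits arise together?** Design effect = 1 + (m − 1)WPC − m × BPC, with m = 12.5 × 0.75 = 9.4 analysed women per period. The article gives no WPC, so 0.025 is an assumption. Starting from the continuity-corrected 460/0.75 = 613.3:
- BPC = 0: 613.3 × (1 + 8.375 × 0.025) = 742.
- BPC = 0.8 × WPC = 0.02: 613.3 × (1 + 8.375 × 0.025 − 9.375 × 0.02) = 627.

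Both limits are therefore reachable as statistical requirements. What fails is the delivery side, pharmacies × periods × recruits.

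**Step 6: effect of the count on power at 737.** Without continuity correction, 737 × 0.75 = 552.75 analysed against 433.6 (unrounded) gives a design effect of 1.275. At BPC = 0 and m = 9.375 this implies WPC = 0.275/8.375 = 0.033. Holding that assumed WPC and BPC = 0:
- 25 pharmacies: m = 552.75/50 = 11.1, power 88.7%.
- 31 pharmacies: m = 552.75/62 = 8.9, power 90.3%.

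**The case against.** The defence is that the target is a total number of women, not a number per site. At a fixed total, more pharmacies mean smaller clusters and a smaller design effect, so moving from about 25 to 31 helps if anything. The pharmacy count is given as approximate, the final total is to be reset from observed data, and the article openly states that equal cluster sizes are a simplification. All of this stands, and it limits the consequence. It does not remove the contradiction: the gap to 737 is 87 women, and rounding of around 25 does not stretch to 28–31.

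A reader might also infer that 626 is wrong, because the article says that "if the BPC equals the WPC then the crossover is as efficient as an individually randomised design" and the uncorrected individual design needs only 579. The documents do not support that. The equality sentence is a general remark about the design, while the Participants section attaches 626 to a BPC close to the WPC, not equal to it. The continuity-corrected figure is 614, and 626 matches 25 pharmacies at 12.5 per period.

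The unstated WPC is a detail that a condensed article may leave to the full protocol. It makes 737 impossible to check here, not wrong. The 29 sites are a dated status report, and the 27 in Box 2 is an interview target that does not enter the sample size, although its wording adds another pharmacy count.

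**Conclusion.** The sample-size inputs contradict both the stated range and the stated design. At around 25 pharmacies, 12–13 recruits per period yield at most 650, which is 12% below the upper limit of 737. At 31 pharmacies they yield at least 744, just above that limit and 118 above the lower one. This part rests only on multiplication of figures in the article.

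A reader might go on to infer that the trial is underpowered. That does not follow. With 31 pharmacies at 12–13 per period the stated total is met, and at a fixed 737 the larger count raises power slightly (88.7% to 90.3%, under the assumed WPC of 0.033 and BPC of zero). Lower power figures could be produced by inserting larger correlations or unequal cluster sizes, but the article supplies no such values. The defect is that the site target and the basis of the 90% power do not describe the design being run.

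**What to change.** Recompute the sample-size basis for the number of pharmacies actually taking part, and use that one count in Study design and setting, Participants and Sample size calculation.

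Restate the per-pharmacy, per-period target so that pharmacies × 2 × target returns the range. If 626–737 is kept, that is about 10.1–11.9 at 31 pharmacies or 10.8–12.7 at 29. Quote the 90% power for that design, with the WPC and the BPC/WPC ratio assumed at each end, and use the matching analysed cluster-period size (recruits × 0.75, or the observed retention) when the final total is set. The Box 2 wording on 27 pharmacies can be aligned in the same edit.

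The cost is one recalculation and changes to a few sentences. The effect size, the outcome and the analysis stay as they are, and the final total was still to be fixed when the article was written.
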